**Prevention of post-splenectomy sepsis (PSS) in patients with asplenia – The PrePSS study protocol**

# Background

The spleen is the largest lymphatic organ and plays a crucial role in linking innate and adaptive immunity. As a result, the absence of the spleen is associated with significant morbidity and mortality (1). Patients with anatomical asplenia (partial or total surgical removal of the spleen) or functional asplenia (loss of function of the spleen) have a significantly increased lifelong risk of severe invasive infections (2, 3). The mortality of post-splenectomy sepsis (PSS, also called overwhelming post-splenectomy infection [OPSI]), the most dangerous complication, reaches 30-50% (4). Studies report incidence rates of 7-8 infections requiring hospitalization per 100 patient-years and a post-splenectomy sepsis incidence of 1 per 100 patient-years. Compared to the general population, patients with asplenia have an approximately 6-fold increased risk of sepsis-related hospitalization (5).

The high mortality of these infections has led to guidelines for the prevention of sepsis in asplenic and hyposplenic patients. These recommendations include patient education, vaccinations, prophylactic and stand-by antibiotics, medical alert cards, travel advice and early treatment of animal bites (6, 7). Patients without a functioning spleen and their physicians should be educated about the everyday risk of overwhelming infections and the need of prompt recognition and treatment of infections.

Asplenic patients should receive pneumococcal vaccination, meningococcal conjugate vaccine, *Haemophilus influenza* type b conjugate vaccine and yearly influenza immunization. A stand-by antibiotic should be prescribed for emergency use (‘pill in the pocket‘). A smaller subgroup of patients (age < 5years, patients after a PSS episode) should obtain antibiotic prophylaxis, although there is no international consensus on when to discontinue prophylaxis. Patients should carry a medical alert that can inform physicians of the patient’s asplenia, optimally. Furthermore, travellers to high-risk areas, for example with regard to malaria, should secure optimal preventive measures. The effectiveness of these prevention measures has been shown in several studies (8-10).

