Aim of the study is to improve the adherence to guideline-based preventive measures and thereby reduce the incidence of PSS by a novel telephone-based intervention that involves both patients and their general practitioners. By educating patients, the intervention contributes to the participation and empowerment of patients, who take responsibility for their own health in general and the implementation of prevention measures in particular. The new intervention is supposed to improve patients’ health by reducing morbidity as well as mortality and increase the quality-of-life of patients with asplenia. In addition, it can be expected that the costs of health insurance companies will decrease, since the treatment and follow-up costs of post-splenectomy infections are relatively high compared to the planned intervention and implementation of preventive measures. Evidence for this assumption can be found in cost-effectiveness analyses of PSS prevention in asplenia registries (12, 21). Furthermore, the development of such an intervention can serve as a model for other studies.

To the best of our knowledge, it is the first study that addresses the insufficient adherence to the prevention recommendations by the development and evaluation of a novel strategy that takes motivational processes into account and involves both patients and physicians.

Our assumption is that a targeted intervention strategy increases the adherence to recommended prevention measures.

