**Methods**

**Aims and hypotheses**

The purpose of this study is to develop, manualize and evaluate a novel intervention that educates both patients and their physicians on appropriate preventive measures that should be undertaken to prevent infections after splenectomy. Besides information provision, the intervention is intended to motivate patients to implement the preventive measures and to convey action-related skills such as planning and managing barriers. It will be evaluated whether this targeted intervention (intervention group) is superior to usual care (historical control group) in terms of primary and secondary study outcomes. More precisely, we have put forward the following hypotheses as to the outcome of the intervention: (a) Adherence to infection-risk reducing preventive measures will significantly be increased (primary outcome). As a result, (b) the incidence of severe infections associated with asplenia (particular PSS) and (c) related health-care costs covered by health insurances will be reduced (distal secondary outcomes). (d) Risk perception, intention to implementation, perceived self-efficacy, action and coping-planning, positive and negative outcome expectations and received social support (HAPA-related variables) expected to account for the effect of the intervention will significantly be enhanced (proximal secondary outcomes). Furthermore, (e) disease knowledge, patients’ general and asplenia-specific self-management, asplenia-specific health literacy, patient involvement as well as health-related quality of life will significantly be enhanced (distal secondary outcomes).

Beside this quantitative outcome-evaluation, intervention patients’ and intervention patients’ physicians’ acceptance and evaluation of the intervention will be inquired in telephone interviews in a process-evaluating part of the study.

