**Sample size considerations**

A priori calculation of the sample size of patient participants to compare the intervention group to the historical control group in the primary outcome was performed with the software ‘*Power and Precision*‘*.* Based on an assumed medium to large effect size of 0.40, a statistical power of 80% and a significance level of 5% (two-sided) the minimum required patient sample of *N* = 100 per group was calculated. Further sample size considerations take into account the actual number of splenectomized patients insured by the AOK. An explorative request showed that 360-400 patients undergo splenectomy a year, resulting in approximately 500 patients assumed to be available for recruitment in the planned inclusion period of 18 months. Based on studies with similar patients (13), we further estimated a proportion of 50% non-respondents for the intervention group and attrition rates of 40% of respondents, so we aim to recruit 500 potential intervention group patients for an expected analysis sample of *N* =178 participants. As this exceeds the statistically required number of cases despite conservative estimations, sufficient cases will be available even after considering potential deceases in the course of the study.

Given that the inclusion period (18 months) is the same for the control group (although retrospectively), sample size considerations for this group are largely the same, with the exception of an assumed proportion of 60% non-respondents and a dropout rate of 50%, resulting in expected *N* = 110 control group cases for analysis. Correspondingly, the number of physician participants included in analysis will be *N* = 178 intervention patients’ physicians and *N* = 110 control patients’ physicians maximum, considering that some patients may have the same physician.

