**Procedure**

The chosen outcomes for patients are measured prior to the intervention (baseline measurement, t0), directly after the intervention (t1) and after a 6-month follow-up period (t2).

At t0, patients in the intervention group are sent paper-pencil pseudonymized questionnaires on baseline proximal and distal secondary outcomes and socio-demographic information. Upon receipt of the filled questionnaires, telephone appointments are arranged with patients for a study physician interview by study nurses. During telephone calls, a vaccination history, use and availability of stand-by antibiotics and the medical alert card are taken to gather baseline data on the primary outcome, the PrePSS-score, along with some other medical information relating to the patients’ asplenia (e.g. indication for splenectomy, splenectomy date and previous episodes of infection or PSS requiring hospitalization)

After t0-data collection, the patient-directed telephone-intervention is implemented. The intervention of the corresponding physician is conducted at about the same time; however, the order is determined by the arrangement of the telephone appointments and not standardized. Secondary physician outcomes are gathered after the physician-directed intervention. Historical control group patients and their physicians go through the same procedure and patients receive t0-questionnaires identical to intervention group patients, but only intervention participants continue measurement after the telephone intervention.

Following each patient telephone call, intervention patients complete post-intervention questionnaires on the proximal secondary outcomes similar to baseline items and evaluate the telephone-intervention (t1).

To test for six-month sustainability of the effects of the intervention they receive follow-up questionnaires on distal secondary outcomes identical to baseline measurement (t2). After return of the follow-up questionnaires, intervention patients are contacted by study physicians via telephone again to inquire the same set of data on the primary outcome and (changes in) medical data, such as the incidence of infections and PSS, gathered at t0.

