**Data analysis**

Demographic characteristics of the study population and effect sizes in the intervention group will be reported descriptively. The main analysis tests the hypothesis that the PrePSS-score at follow-up is higher (better adherence to infection-risk reducing preventive measures) in the intervention group than in the control group. Due to the non-randomized design a propensity score adjustment is performed to reduce potential bias that may be caused by differences on covariates in the two groups (36). We will apply general linear models with propensity score as a covariate. The same method will be used for the analysis of secondary outcomes. Assuming missing data in the questionnaires, multiple imputation will be considered for corresponding analyses. Additional analyses will be conducted with structural equation modeling technique to test a priori specified mediation models of intervention effects.

A cost-effectiveness analysis of the intervention will be conducted by analyzing the change-from-baseline scores of the primary and the secondary outcomes in relation to the costs of the intervention. To reveal the economic efficiency of the intervention, routine data will be used to determine standard treatment and follow-up costs associated with infections requiring hospitalization and with PSS in asplenic patients to contrast them to the intervention costs.

In the qualitative analyses, the audio files of the interviews will be transcribed by an external service provider and the transcripts will be analyzed using a qualitative content analysis.

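### PSS incidence is collected only from patients alive to be interviewed, so fatal PSS drops out of the comparison in hypothesis (b)

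*Protocol*

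**What the plan says.** Under Aims and hypotheses, hypothesis (b) is that the intervention reduces "the incidence of severe infections associated with asplenia (particular PSS"), classed as a distal secondary outcome.

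The Procedure section gives the source of these events. At t0 the study physician's telephone interview asks patients in both groups about "previous episodes of infection or PSS requiring hospitalization". At t2, intervention patients who have returned the follow-up questionnaire are telephoned again about changes in "medical data, such as the incidence of infections and PSS, gathered at t0". Controls are not measured after t0. The patient's account is confirmed with the treating physician at t0 and, in the intervention group, at t2.

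Under Participants and recruitment, controls are patients more than 6 and at most 18 months past splenectomy. Intervention patients are approached about 6-8 weeks after surgery and are at most 4 months past it.

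The Background gives "a post-splenectomy sepsis incidence of 1 per 100 patient-years". On the mortality of PSS it writes "the most dangerous complication, reaches 30-50" (per cent). It also expects the intervention to improve patients' "health by reducing morbidity as well as mortality".

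Deaths are mentioned only in Sample size considerations, as a loss of cases: "sufficient cases will be available even after considering potential deceases in the course of the study".

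Insurer routine data have two stated uses. One is a group-level check on vaccinations and emergency antibiotics (Outcome measures). The other is costing, where "routine data will be used to determine standard treatment and follow-up costs associated with infections requiring hospitalization and with PSS" (Data analysis). Neither is described as a source of PSS incidence or of deaths by group.

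**The concern.** An interview can record only the PSS that a patient survived. By the protocol's own mortality figure, between a third and a half of the event named in hypothesis (b), roughly speaking, falls outside the described data collection. Analysis cannot recover events that were never collected.

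The survival condition also differs between the groups. A control must live until contacted, more than 6 and up to 18 months after surgery. An intervention patient must live until recruitment a few weeks or months after surgery, and then to t2.

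Several parts of the intervention act after an infection has begun: recognising symptoms, seeking care quickly, stand-by antibiotics and the alert card. They could therefore change case fatality as well as incidence. If they do, a PSS that would have been fatal and unrecorded becomes a survived and recorded one, and the interview count moves against the intervention. The protocol also states no reporting of deaths by group that would show this.

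**Working it through.** **The protocol's own figure.** The protocol gives no expected number of PSS events. Its only power calculation is for the primary outcome: n = 2 × (1.960 + 0.842)² / 0.40² = 98.1, so 99 per group. The t-based solution is 99.08, so 100, and the stated 100 per group is reproduced. The present point does not depend on it.

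**Inputs.** From the Background: PSS incidence 1 per 100 patient-years, PSS mortality 30-50%. From Sample size considerations: expected analysis samples of 178 (intervention) and 110 (control). From Procedure: 6-month follow-up. From Participants and recruitment: the control window of 6 to 18 months.

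**1. Recorded rate.** If fatal PSS goes unrecorded, the recorded rate is the true rate × (1 − case fatality):
- fatality 0.30: 1.0 × 0.70 = 0.7 per 100 patient-years
- fatality 0.50: 1.0 × 0.50 = 0.5 per 100 patient-years

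**2. Recorded ratio, intervention to control.** Let r be the relative reduction in true incidence, and c0 and c1 the case fatality in control and intervention patients. Then

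recorded ratio = (1 − r) × (1 − c1) / (1 − c0), against a true ratio of 1 − r.

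If c1 = c0, the fatality terms cancel and the recorded ratio is 1 − r. If fatality is halved (c1 = c0/2):

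| c0 | r = 0 (true ratio 1.00) | r = 0.25 (true ratio 0.75) | recorded count rises only if r is below |
|---|---|---|---|
| 0.30 | 0.85/0.70 = 1.21 | 0.75 × 1.21 = 0.91 | 1 − 0.70/0.85 = 0.18 |
| 0.40 | 0.80/0.60 = 1.33 | 0.75 × 1.33 = 1.00 | 1 − 0.60/0.80 = 0.25 |
| 0.50 | 0.75/0.50 = 1.50 | 0.75 × 1.50 = 1.125 | 1 − 0.50/0.75 = 0.33 |

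**3. Expected events in groups of the analysed size.** Events = N × years × 0.01; the fatal share is 30-50% of these.
- Intervention, 6 months: 178 × 0.5 × 0.01 = 0.89 PSS, of which 0.27-0.45 fatal. Counted from splenectomy to t2 with entry at 4 months (10 months, 0.83 years): 1.48 PSS, 0.44-0.74 fatal.
- Control, 1 year since surgery (assumed midpoint of the window): 110 × 1.0 × 0.01 = 1.1 PSS, 0.33-0.55 fatal. Over 0.5 to 1.5 years: 0.55-1.65 PSS, 0.17-0.83 fatal.

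The stated response and attrition rates applied to 500 candidates give 500 × 0.5 × 0.6 = 150 and 500 × 0.4 × 0.5 = 100 rather than 178 and 110. With those numbers the expected PSS are 150 × 0.5 × 0.01 = 0.75 and 100 × 1.0 × 0.01 = 1.0, which changes nothing here.

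**The case against.** **The intervention is meant to prevent PSS, not only to make it survivable.** This stands. A reader might infer that an intervention which saves lives is bound to show more PSS. The protocol does not support that. If lives are saved by preventing PSS, the recorded count falls. If case fatality is equal, the ratio is undisturbed. A rise needs a fall in fatality that outweighs the fall in incidence: with fatality halved, the incidence reduction must be below 18-33%. The reversal is possible, not certain.

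**The routine data already cover PSS.** This stands in part. A reader might infer that the economic comparison also rests on survivors, or that fatal PSS is counted nowhere. The Data analysis section takes the costs of PSS and hospitalised infections from routine data and does not limit these to survivors or interviewees. What is missing is a stated use of these data for incidence by group.

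**The physician is a second source.** This is true for interviewed patients: physicians may be interviewed first and may report something different. The text describes confirmation of the patient's account and says nothing about contacting the physician after a death, so the gap remains.

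**Mortality is not among hypotheses (a) to (e), and deaths are foreseen.** Also true. Lower mortality is an expectation in the Background, not a study outcome. The fair point is only that no reporting of deaths by group is stated.

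**The numbers are tiny.** This stands and limits the severity. One could apply the incidence to about 500 control candidates and arrive at several PSS, but most of those candidates are not expected to be analysed. In groups of the analysed size, fewer than one fatal PSS is expected in each.

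**Conclusion.** The point holds as one about ascertainment. As described, the PSS incidence in hypothesis (b) comes only from surviving patients' interviews with physician confirmation, so fatal PSS, 30-50% of PSS by the protocol's own figure, is missed in both groups over survival windows that differ.

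Both recorded rates are then too low (0.5-0.7 in place of 1 per 100 patient-years). Their ratio is not biased by this mechanism if case fatality is equal. If the intervention lowers case fatality, the comparison is biased against it and could reverse: a recorded ratio of 1.21-1.50 with fatality halved and incidence unchanged.

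This assumes that no fatal PSS is recorded, and it ignores deaths from other causes and the patient-time lost to death. Halved fatality is an illustration; the protocol gives no expected effect on fatality. It also takes incidence and fatality as constant over time since surgery. If they are not, the unequal windows add a further difference that the protocol's figures cannot size.

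Severity is minor to moderate. The outcome is secondary, about one PSS is expected per analysed group, and the PrePSS-score analysis does not use these counts.

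**What to change.** **In Procedure and Data analysis:**
- Label interview-based counts of infections and PSS as non-fatal events among survivors.
- Report the known deaths of enrolled participants by group.

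**As a supplementary comparison:** extend the existing group-aggregated insurer query to deaths, PSS and infections requiring hospitalisation. Cover all patients identified in the database search, including those who died, did not respond or were lost, over the same window since splenectomy in both groups. Present this beside the participant data, not in place of it.

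**Cost:** the labelling and the report of deaths need only text and a table. The query is one addition to data that the insurer already supplies, for patients it already identifies. Its limits should be stated:
- Claims coding of PSS is imperfect.
- Aggregated data allow no individual adjustment, so the propensity score cannot be applied.
- Any effect is diluted, because non-respondents in the intervention-period cohort (assumed to be 50%) did not receive the patient intervention. The result compares two cohorts, not treated with untreated patients, and should be labelled as such.

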***Physician-directed intervention***

The physician-directed telephone intervention comprises evidence-based information on the consequences of asplenia and the increased infectious risk associated with high mortality rates. Attending physicians are educated about preventive measures consistent with current post-splenectomy guidelines including currently recommended vaccination and revaccination on the basis of given immunization schedules, indication of stand-by antibiotics and antibiotic prophylaxis. Furthermore, the intervention session includes an introduction in the purpose and use of the medical alert card and the necessity of patient education, particularly as to the patient-initiated antibiotic use in case of febrile illness. Physicians are advised to document any antibiotics in use and record a vaccine plan (vaccination status, need and interval for revaccination) specific to their patient using provided fields on the medical alert card.

The objective of the intervention is to heighten practitioners’ awareness and knowledge of available preventive measures to improve guideline-based post-splenectomy care. Thereby the information-provision component is the integral part of the physician’s intervention. However, in line with the patients’ intervention, the physicians’ intervention also targets risk perception, positive outcome expectancy and, subsequently, motivation to follow guideline recommendations. But practitioners are not obligated to do so and it is made sure that they do not feel restricted in their freedom of decision.

The intervention sessions take approximately 10 minutes. All participating physicians receive the intervention irrespective of the group allocation of their patients.

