To ensure a valid data basis, patients’ self-report data on the primary outcome variable and on the medical information are confirmed with the corresponding physician both at t0 and (in the intervention group) at t2. In case physicians are interviewed prior to their patients, patients are made aware of any discrepancies between their information and information their physicians provided when required.

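### The primary comparison sets an intervention score from a second physician-confirmed look (t2) against a control score from one look (t0), so vaccinations missed at t0 can be credited in one group only

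*Protocol*

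**What the plan says.** Protocol, Data analysis: the main hypothesis is that the PrePSS-score at follow-up is higher in the intervention group than in the control group, tested in a general linear model with the propensity score as covariate.

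Protocol, Procedure: both groups give a vaccination history at t0, but "only intervention participants continue measurement after the telephone intervention". At t2 the study physicians telephone the intervention patients again "to inquire the same set of data on the primary outcome and (changes in) medical data". The patients' reports "are confirmed with the corresponding physician both at t0 and (in the intervention group) at t2".

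Protocol, Physician-directed intervention: "Physicians are advised to document any antibiotics in use and record a vaccine plan (vaccination status, need and interval for revaccination") on the alert card. This advice goes to physicians of both groups.

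Protocol, Primary outcome and Table 1: the score is built from what patient and practitioner report by telephone. The pneumococcal and meningococcal items carry 0-3 points each, and the stand-by antibiotic and alert card items 0-2 each, for a maximum of 10. Health insurance data aggregated by group are to be used to validate the self-report. Exact score formation is in a supplement that is not part of the document at hand.

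**The concern.** The vaccination items score whether doses were received, but the information comes from recall and practice records. A dose given in hospital or by another doctor may be unknown to both informants at t0. In the intervention group there is a second chance to find it six months later, when the patient knows which vaccinations matter and the physician has been advised to write the status down. In the control group there is no second chance. Part of the group difference could then reflect a more complete record in one group and not more vaccination.

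This needs no dishonest reporting or biased scoring. The propensity score balances covariates, whereas the number of looks is fixed by group, so there is nothing for it to adjust on. The same error would enter the change-from-baseline scores that the cost-effectiveness analysis uses.

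**Working it through.** **1. The plan's own figure.** Sample size considerations gives an "assumed medium to large effect size of 0.40, a statistical power of 80% and a significance level of 5% (two-sided") and states that "the minimum required patient sample of *N* = 100 per group was calculated". Normal approximation: n = 2 × ((1.960 + 0.842)/0.40)² = 98.1, so 99 per group. The t-test version gives 99.08, so 100. The stated figure reproduces, and this point does not touch it. The effect of 0.40 SD serves below as the yardstick.

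**2. Number of looks at the scores compared.**

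| | Intervention | Control |
| --- | --- | --- |
| Score used in the primary test | t2 | t0 |
| Vaccination history taken | t0 and t2 | t0 |
| Confirmed with physician | t0 and t2 | t0 |
| Education and documentation advice before the final look | yes | order of calls not standardized; the patient's own session comes after data collection |

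The document nowhere limits t2 credit to doses given after t0, and nowhere provides for comparing the two groups at an equal number of looks.

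**3. Points exposed.** 3 (pneumococcal) + 3 (meningococcal) = 6 of 10.

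**4. Size under stated assumptions.** The protocol gives neither an SD for the score nor a rate of missed doses, so both are assumed here: SD 2.5 (range 2 to 3), and 5% or 10% of patients with a pre-t0 dose that surfaces only at t2, worth 1.5 or 3 points. The group sizes are the protocol's: "expected analysis sample of *N* =178 participants" and, for controls, "resulting in expected *N* = 110 control group cases for analysis".

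- Spurious shift = share of patients × points credited; d = shift / SD.
- Noncentrality = d × √(178 × 110 / 288) = d × √67.99 = d × 8.245.
- Probability of rejection with no true effect = two-sided 5% test from the noncentral t with 286 degrees of freedom (critical value 1.968).

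| Share | Points | Shift | d (SD 2.5) | Share of 0.40 | Noncentrality | P(reject) |
| --- | --- | --- | --- | --- | --- | --- |
| 5% | 1.5 | 0.075 | 0.03 | 8% | 0.247 | 5.7% |
| 10% | 1.5 | 0.15 | 0.06 | 15% | 0.495 | 7.8% |
| 10% | 3 | 0.30 | 0.12 | 30% | 0.989 | 16.7% |

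Sensitivity to the SD, for 10% and 3 points at 178 versus 110: SD 3 gives d = 0.10 and 13.0%; SD 2 gives d = 0.15 and 23.4%.

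To produce the whole planned effect at 3 points each, the share would have to be 0.40 × SD / 3: 27% at SD 2, 33% at SD 2.5, 40% at SD 3.

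These figures do not net out doses withdrawn at t2, or patients whose missed dose was followed by a new vaccination that earns the points legitimately. Both would reduce the shift.

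**The case against.** The case against is substantial, and much of it stands.

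- **The first look is not weak.** Data at t0 are already confirmed with the physician in both groups, so only doses missed by both informants matter. This limits the size and does not remove the asymmetry.
- **A reader might infer that only intervention patients received the vaccination plan, between the two looks.** The Intervention section says otherwise: plan and alert card go to all participants before the intervention. Physician education is also independent of group, and because the order of calls is not standardized, some control physicians may be advised before the patient's call. What remains specific to the intervention group is the second look itself.
- **A reader might infer that every old dose found at t2 is false adherence.** In the primary contrast, a genuine dose found late makes the t2 score more accurate; the error lies in control scores that stay under-recorded. Wrongly counted gain describes only the change-from-baseline analysis.
- **A reader might infer that the primary test is badly inflated.** If 20% of patients gained 3 points, rejection with no true effect would be about 50%. Nothing in the document supports that rate, and a single missed dose of a sequential pneumococcal schedule is unlikely to earn the full 3 points.
- **The insurance data could help.** They do not depend on how often anyone was interviewed, and could show a group-level gap between reported and billed vaccinations. Being aggregated by group, they can flag the problem but cannot correct individual scores.
- **The supplement may contain dating rules.** That is possible and cannot be checked here.

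**Conclusion.** The point holds as a measurement asymmetry: two physician-confirmed looks in the intervention group against one in controls, in up to 6 of 10 primary points and beyond the reach of propensity adjustment. The direction probably favours the intervention, but is not certain, because a second look can also withdraw a dose wrongly claimed at t0.

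The size is not known. With modest assumptions (5-10% of patients, 1.5 points, SD 2.5) the distortion is 0.03-0.06 SD and the error rate about 6-8%, which is small. With 10% and 3 points it is 0.12 SD, 30% of the planned effect, and about 17%. That range justifies a sensitivity analysis. It does not support the conclusion that the primary analysis is invalid or that a positive result would be an artefact.

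**What to change.** Keep the planned primary analysis and prespecify one sensitivity analysis with the same propensity-adjusted model, on a score that allows one look per vaccination:

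- Vaccinations dated before t0 keep the status they had at t0.
- Vaccinations dated after t0 count as found at t2.
- The stand-by antibiotic and alert card items are scored as planned, because they measure current availability and carrying.

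Report the number of pre-t0 doses first found, and the number withdrawn, at t2. If the two analyses differ materially, qualify the superiority conclusion.

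Agreement of the two analyses should not become a second condition for superiority. That would cost power, and the restricted score has its own errors: a sequence whose first dose was discovered late but was truly completed after t0 would be scored incomplete, and a dose wrongly claimed at t0 would keep its credit. The discovery rate at t2 should not be read as a direct estimate of what was missed in controls. They are more than 6 and at most 18 months from splenectomy, against at most 4 months for intervention patients, so recall and records may differ.

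Cost: one derived score and one extra model run, with no new patient contact. It requires dose dates from the vaccination history, which the protocol does not explicitly say are collected. The sensitivity estimate may be slightly smaller than the primary one.
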